#### Phase 2 sampling & data collection

During Phase 2 of the study, the randomized control trial, researchers and research assistants will randomly recruit women attending an antenatal care visit and their partners, inviting them to participate in the randomized control trial. Every participant will be required to provide informed consent before they can be included in the sample. Participants will be randomized into either the intervention group or the control group until the sample size of 420 has been reached. To implement the randomization, a table with the generated randomization sequence will be used, and as a participant agrees to participate in the study, they will be sequentially allocated to a row in the table that will determining the group that the participant will form part of. The sample size for the randomized control trial, was determined using the primary outcome of the study, change in knowledge. We will allocate participants equally to the treatment and control groups, through a balanced computer-generated random sequence. We use a 0.05 level of significance (*P* < 0.05) and a power of 0.9 with a two tailed test for significance.

Our hypothesis is that at the 3-month follow-up, participants in the control group will score 43% on the intention to change behavior score (12 points out of 28 points in the survey). We propose that after the 3-month follow-up the intervention group will score 61% (17 out of 28 points). This is an 18% absolute increase and a 1.41 times relative increase. A sample size of *n* = 140 was calculated for the intervention group and the control group. We then used an increase of 50% to account for potential participant drop-outs, bringing the sample size for the intervention group to *n* = 210 and the sample size for the control group to n = 210, spread equally and randomly across the two sites (Kgabo CHC[urban site] and Ga-Rankuwa[rural site]). Thus, a total of *n* = 420 participants for the entire randomized control trial will be required. These sample size calculations were carried out on G-Power 3.1.9.6.

Sample size calculations were based on the difference between two independent proportions using a z-test (Power: 0.9, Alpha 0.05, Allocation N1/N2: 1, p1 = 0.43, p2 = 0.61). The sample size per group was rounded up to the nearest 10 patients (N1 = 140, N2 = 140).

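### 140 per group does not follow from the stated two-tailed calculation: 90% power needs 160 completers per group, and 140 give 86%

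*Protocol article*

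**What the plan says.** All of this stands in the protocol article under Methods, *Phase 2 sampling & data collection*.

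- **Level, sidedness and power:** "We use a 0.05 level of significance", with "a power of 0.9 with a two tailed test for significance".
- **Method:** "Sample size calculations were based on the difference between two independent proportions using a z-test".
- **Inputs as listed:** "Power: 0.9, Alpha 0.05, Allocation N1/N2: 1, p1 = 0.43, p2 = 0.61". This line does not repeat the number of tails.
- **Origin of the two rates:** controls are expected to "score 43% on the intention to change behavior score (12 points out of 28 points in the survey"), and it is proposed that "the intervention group will score 61% (17 out of 28 points").
- **Result:** "The sample size per group was rounded up to the nearest 10 patients (N1 = 140, N2 = 140").
- **Allowance for loss:** "We then used an increase of 50% to account for potential participant drop-outs", which takes 140 to 210 per group and 420 in total.

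Under *Phase 2 data analysis* the article sets significance at 5% and reports 95% confidence intervals, which agrees with a two-sided 5% test. Nothing in the article supports a one-sided hypothesis.

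**The concern.** The paragraph prints every input needed to reproduce the calculation, and the printed result does not match them. For a difference of 18 percentage points around 50%, 140 per group is too small for a two-sided 5% z-test at 90% power, but it is what a one-sided test gives after rounding.

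At stake are the power claim and the retention target. A team that believes 140 completers per group secure 90% power could accept the loss of a third of those enrolled. That loss is a practical possibility: the outcome comes from a telephone survey at 3 months, and the article discards the data of participants who discontinue or deviate.

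**Working it through.** **Inputs**, all from *Phase 2 sampling & data collection*: p1 = 0.43, p2 = 0.61, difference 0.18, allocation 1:1, alpha 0.05, power 0.90.

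**Formula** (z-test for two independent proportions, pooled variance under the null), per group:

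n = [z_a × √(2·p̄·(1 − p̄)) + z_b × √(p1·q1 + p2·q2)]² / (p2 − p1)²

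- p̄ = (0.43 + 0.61)/2 = 0.52, so √(2 × 0.52 × 0.48) = √0.4992 = 0.7065
- p1·q1 + p2·q2 = 0.2451 + 0.2379 = 0.4830, square root 0.6950
- z_b = 1.2816 for 90% power

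**Reproducing the stated 140.** One-tailed, z_a = 1.6449:

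n = (1.6449 × 0.7065 + 1.2816 × 0.6950)² / 0.0324 = 130.1, so 131. Rounded up to the next 10, this is 140, the stated figure.

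**The test the article names.** Two-tailed, z_a = 1.9600:

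n = (1.9600 × 0.7065 + 1.2816 × 0.6950)² / 0.0324 = 159.8, so 160. The stated 140 is 20/160 = 12.5% short.

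**Does another formula rescue 140?** Sizes per group at 90% power, before rounding to the next 10:

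| Version | Two-tailed | One-tailed |
|---|---|---|
| Pooled | 160 | 131 |
| Unpooled | 157 | 128 |
| Arcsine | 161 | 131 |
| Pooled under both hypotheses | 162 | 132 |
| Continuity-corrected | 171 | 141 |
| Pooled, unrounded 12/28 and 17/28 | 163 | 133 |

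Every two-tailed version rounds up to 160 or more.

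**Power at the stated size.** Power = Φ[(0.18 × √n − z_a × 0.7065)/0.6950].

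- n = 140, two-tailed: Φ[(0.18 × 11.832 − 1.96 × 0.7065)/0.6950] = Φ(1.072) = 85.8%. Exact enumeration of the z-test gives 85.5%; the formula with 12/28 and 17/28 gives 85.2%.
- n = 140, one-tailed: 91.8%
- n = 160, two-tailed: 90.0%
- n = 210 (no loss), two-tailed: 96.1%

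**Tolerable loss from 210 per group.**

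- Down to 140: (210 − 140)/210 = 33.3%, the loss that the 50% increase absorbs
- Down to 160: (210 − 160)/210 = 23.8%, the loss that keeps two-tailed 90% power

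Applying the same 50% increase to 160 would give 240 per group, 480 in total.

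**The case against.** **The one-tailed origin is inferred.** The article never says one-tailed. A two-tailed run at 85% power gives 137, which also rounds up to 140. This stands as a caution about the cause. One-tailed is the likelier reading, because power 0.9 is stated twice while the number of tails is missing from the input line. Either way, 140 is not the two-tailed 90% figure.

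**A one-third loss is not a stated plan.** The article gives no expected drop-out rate; 33.3% is only what 210 can lose and still leave 140. That is fair, and the corrected text should not call it planned. It is nevertheless the loss that the stated allowance covers.

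**The effect on the enrolled sample is modest.** With 210 per group, two-tailed power is 96% with no loss and 91% at 20% loss. This stands: enrolling 420 is not underpowered in itself. (The registration data set in the article gives a target of 450; 225 per group could lose (225 − 160)/225 = 28.9%.)

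**The binary model may not suit the outcome.** The 43% and 61% are mean scores out of 28, and a score bounded between 0 and 1 cannot have a variance above p(1 − p), so a comparison of mean scores may well have more power. Under a normal approximation with independent participants, 140 per group would keep two-sided 90% power unless the score SD exceeded about 0.465 (13 of 28 points). At an assumed SD of 0.3 (8.4 points), power would be above 99%. The article gives no SD. This limits what 86% says about the trial's true power, but it does not make 140 the right answer to the calculation the article describes. Nor does the paragraph's use of the intention score, when it says the size rests on knowledge. Both are separate questions.

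**Conclusion.** The concern holds. A two-tailed two-proportion z-test with the article's own inputs needs 160 completers per group for 90% power. The stated 140 is 20 per group short and gives 85.8%, a shortfall of 4.2 points. The loss compatible with 90% power at 210 enrolled per group is 23.8%, about 10 points less than the paragraph implies.

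This takes the two-proportion z-test, the rates 0.43 and 0.61 and 1:1 allocation as given, and treats the words two tailed as the intent, which the 5% level and 95% intervals support. The 160 applies to the named z-test. The article also reports a Fisher's exact P-value for all associations; under the same two rates, a two-sided Fisher test has 82.6% power at 140 per group and 87.9% at 160. That the cause was a one-tailed setting is probable, not proven, and the conclusion does not depend on it.

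**What to change.** In *Phase 2 sampling & data collection*:

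1. Add the number of tails to the input line and replace 140 by 160 per group: two-sided 5%, 90% power, 160 completers per group (320 in total).
2. Keep 210 per group and 420 in total, but describe the allowance correctly: at least 90% power if loss is at most 23.8%, and about 86% if loss reaches one third.
3. Set the retention target for the 3-month telephone survey at 160 completers per group.

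If the authors want to keep a full 50% increase over the requirement, the figures become 240 per group and 480 in total; this is a choice, not a necessity.

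The cost is one reworded paragraph and a less generous stated tolerance for loss. Design, analysis and the 420 enrolled do not change.

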### Study site

The study sites are two high volume community health centers (CHC) in the Tshwane district of Gauteng province in South Africa, FF Ribeiro Clinic and Kgabo CHC. FF Ribeiro Clinic is situated in the central business district of Tshwane, catering to an urban community and Kgabo CHC, is situated in a large settlement, Ga-Rankuwa, catering to a semi-rural community.

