	Ask about ANC			
	Own HIV status known			
	Partners HIV status known			
	Discourage alcohol			
	Encourage wash hands			
	Encourage wear a mask			
	Encourage breastfeeding			
	Provide green vegetables			
	Provide fruit			
	Provide meat			
	Attend birth			
	Encourage fetal kick feel			
	Take vaccination			
	Encourage hold baby			
**Knowledge Score**	Skin to skin KMC			
	Breastmilk prevent infections			
	Breastmilk alone			
	Breastmilk and water			
	Formula feeding			
	Traditional tea/muti			
	Avoid alcohol			
	Source of iron			
	Enough iron			
	Cows milk			
	Postnatal care			
	Condom			
	HIV medication			
	HIV positive breastfeeding			
	Stop breastfeeding			
	Vaccines protect			
	Dangerous vaccines			
	Difficulty sleeping			
	Severe headaches			
	Baby kicks			
	Bleeding			
	Newborn loose weight			
	Newborn fever			
	Cries a lot			
	Black stools			
	Visit clinic			
	Excercise			
	Solid foods			
**User Satisfaction**	Easy to understand			
	Useful			
	Difficult to watch			
	Download easy			
	Download time			
	Follow information			
	Identify with characters			
	All information needed			

Results will be reported by comparing video intervention arm and treatment as usual across rural and urban sites and by outcome sub-groupings (see mock Table 3). Statistical significance will be set at 5% and results will be presented with 95% Confidence Intervals. A Fisher’s exact *P*-value will be reported for all associations.

**Table 3 Tab3:** Mock table of results reporting

Outcome Analysis	Urban				Semi-rural				Overall			
Variable Groupings:	Video Intervention	TAU ANC Brochure	RR (95%CI)	*P*-value	Video Intervention	TAU ANC Brochure	RR (95%CI)	*P*-value	Video Intervention	TAU ANC Brochure	RR (95%CI)	*P*-Value
Behavioural intentions Mothers												
Behavioural intentions Partners												
Knowledge Score												
User Satisfaction												

Relative Risk calculated using Poisson Regression (rate of correctly answered questions over total questions)

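### The allocation procedure described does not ensure the stated equal spread of each arm over the two sites

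*Protocol article*

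**What the plan says.** All of this is in the Protocol article.

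- **Target** (Phase 2 sampling & data collection): 210 per arm, "spread equally and randomly across the two sites".
- **Sequence** (same section): "We will allocate participants equally to the treatment and control groups, through a balanced computer-generated random sequence". Balance is promised between arms; site is not mentioned.
- **Device** (same section): "a table with the generated randomization sequence will be used", and as each person agrees, "they will be sequentially allocated to a row in the table that will determining the group that the participant will form part of".
- **Stop** (same section): "Participants will be randomized into either the intervention group or the control group until the sample size of 420 has been reached".
- **Use of site** (Phase 2 data analysis): the arms are compared "across rural and urban sites and by outcome sub-groupings". Mock Table 1 sets out the confounders by arm within each site, with P-values. Mock Table 3 gives a relative risk, confidence interval and P-value for urban, semi-rural and overall. The effect measure is a relative risk from a Poisson regression without adjustment.

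**The concern.** The section states a site-by-arm target and also describes how people are allocated, but no step in that description leads to the target. Row order and a total of 420 control the arms. They do not control how many people come from each clinic, or how the arms fall within a clinic.

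Site matters because the results tables compare the arms within each clinic. An uneven site split weakens the smaller clinic's comparison. A chance arm imbalance within sites also lets any difference in knowledge between the clinics add noise to the overall relative risk, because no site term is planned.

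**Working it through.** **The plan's own figures.** 140 × 1.5 = 210 per arm; 210 × 2 = 420 in total; 210 / 2 sites = 105 per arm per site, or 210 per site. This chain is correct. (Whether 140 follows from the stated power inputs is a separate matter and has no bearing here.)

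**Assumptions.** Both clinics draw on one list of 210 video and 210 control rows, and people from the two clinics arrive interleaved at random. The article does not state the first assumption. It gives no clinic recruitment rates, so the site shares below are assumed.

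**1. Arm split within a site, site totals equal at 210.** The video count at a site is hypergeometric: 210 draws from 420 rows, of which 210 are video.
- Mean = 210 × 210/420 = 105.
- SD = √[210 × 0.5 × 0.5 × (420 − 210)/(420 − 1)] = √26.3 = 5.13.
- 95% range: 95 to 115.
- Probability that the arms at a site differ by 10 or more: 38%; by 20 or more: 6%.

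**2. Site totals, with only the total of 420 as the stop.** Simulation, 200,000 runs for each share:

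| Assumed share | Expected per arm at the two sites | All four cells within 10 of 105 |
|---|---|---|
| 50:50 | 105 and 105 | 73% |
| 60:40 | 126 and 84 | 0.5% |
| 67:33 | 140 and 70 | about 0 |
| 75:25 | 157.5 and 52.5 | about 0 |

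At 50:50 the site total has SD √(420 × 0.5 × 0.5) = 10.2 and a 95% range of 190 to 230. All four cells equal exactly 105 in 0.3% of runs.

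**3. Precision at the smaller site.** With the same spread of scores and the same retention, the standard error scales as 1/√n. At 60:40 it is √(105/84) = 1.12 times that of the equal split, about 12% wider. At the larger site it is √(105/126) = 0.91 times.

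**4. Effect on the overall comparison.** Let D be the difference in mean score between clinics and k the video count at a site of 210. The unadjusted arm difference shifts by D × (2k − 210)/210.
- For an assumed D of 10 percentage points and k = 115: 10 × 20/210 = 0.95 point.
- SD of the shift: 10 × 2 × 5.13/210 = 0.49 point.
- For scale, the planned difference is 61% − 43% = 18 points.
- Treating the outcome as yes/no, as the sample size calculation does, with 140 per arm its standard error is √[(0.43 × 0.57 + 0.61 × 0.39)/140] = 5.9 points.

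**The case against.** The phrase about equal spread can itself be read as a site target of 210, and a condensed article may leave lists per site and closing rules to the full protocol. The article never says that the clinics share one list; that is inferred from the singular noun. Unstratified 1:1 allocation of 420 people is valid, and at similar recruitment rates the spread would come out roughly equal.

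Most of this stands, and it limits the point. It does not remove it. The article did not leave the mechanism out: it gives the device, the order of filling and the stop, and none of these refers to site. Calling the spread both equal and random leaves open whether it is a rule or an expectation.

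Three stronger readings are tempting, and the document does not support them:

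- *The procedure cannot deliver the spread, and two clinics will use rows twice or out of order.* This needs a shared table in a particular physical format, which is not described. On the shared-list reading there is still a 73% chance that all four cells fall within 10 of 105 when the clinics recruit at equal rates.
- *The overall relative risk is biased.* Chance imbalance under randomisation is random error. Its effect is under 1 point at the edge of the 95% range, for an assumed 10-point clinic difference.
- *Power at the smaller site falls to 38% from 57%.* These figures assume 70:30 recruitment (42 against 70 completers per arm) and treat a score as one yes/no result per person. For a 5-point difference out of 28 with 42 per arm, a t-test has power of about 0.90, 0.62 or 0.37 at assumed SDs of 7, 10 or 14 points. The 38% is thus close to a worst case, the article gives no SD, and it claims no power by site.

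**Conclusion.** The point holds as a minor one: the described procedure does not ensure the equal spread that the same section states. If one list serves both clinics, chance alone gives 95 to 115 video participants at a site of 210. Unequal recruitment moves the site totals much further, to 126 against 84 per arm at an assumed 60:40. The consequences are a less precise comparison at the smaller site (standard error about 12% larger at 60:40) and a small random error overall (SD about 0.5 point for an assumed 10-point clinic difference). The overall 210:210 balance and the power of the overall comparison do not depend on it. The size rests on the shared-list reading and the assumed recruitment shares; the absence of any site step in the description does not.

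**What to change.** 1. Generate one balanced 1:1 list per site, for example in permuted blocks of varying size, and say so in the section.
2. Choose one of two rules for the site totals. Either close each list at 210, so that every site-by-arm cell is 105 by construction and the total stays 420. Or delete the word equally and let the totals follow recruitment; each list then needs more than 210 rows, and blocking keeps the arms close to equal wherever it stops.
3. Include site as a term in the overall Poisson model. The unadjusted relative risk can be shown beside it.
4. While editing that sentence, reconcile its site names. It labels Kgabo CHC as urban and gives Ga-Rankuwa as the rural site, whereas Study site places Kgabo CHC in Ga-Rankuwa, serving a semi-rural community, and describes FF Ribeiro Clinic as the urban one.

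The cost is a regenerated sequence, one model term and a few words of text. Closing each list at 210 has one real downside: recruitment lasts until the slower clinic fills. The registration data set lists 29 people enrolled without giving the phase; anyone already randomised keeps their allocation.

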### Study population

The study population includes expectant mothers, 18 years or older attending antenatal care services, pregnant women’s partners, and health workers. Expectant mothers without partners will not be excluded from participating in our study.

The inclusion criteria for expectant mothers and their partners include:Expectant mothers and their partners must be 18 years and older.Expectant mothers must be accessing antenatal care services at either FF Ribeiro Clinic or Kgabo CHC.Expectant mothers and their partners must provide informed consent to participate in the study.

The inclusion criteria for health workers include:Health workers must be 18 years and older.Health workers must be knowledgeable about antenatal care and work with mothers and their partners.Health workers must provide informed consent to participate in the study.

There are no specific exclusion criteria beyond the inclusion criteria.

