#### Phase 1 sampling & data collection

During Phase 1, purposive sampling will be used to select women and their partners attending antenatal care visits at the study sites for in-depth interviews. Health workers will be purposively selected based on their designated positions. Selected health workers could include community health workers, maternal-child health decision makers or experts, CHC managers, maternity and neonatal unit managers and sub-district or district managers of maternal, neonatal and child health programs. Only participants who provide informed consent to participate in the first phase of the study will be interviewed. The interview guide used during Phase 1 is presented in Additional file 1: Annexure 1.

In-depth interviews will be conducted with 10-15 pregnant women, who present for an antenatal care visit at the study sites. Additionally, in-depth interviews will be conducted with 10-15 health workers at the study sites. A semi-structured questionnaire will be used to guide the qualitative interviews of Phase 1.

The researchers will recruit expectant mothers and their partners after they present at the study sites for an antenatal care visit and will explain the purpose of the study. Expectant mothers who show an interest in participating in the qualitative study will be screened to assess if they meet the inclusion criteria. Informed consent will then be obtained from eligible expectant mothers and their partners. Researchers and research assistants will conduct the interviews in a private area at the respective study sites. All participants will receive ZAR 100 to compensate them for their time and expenses incurred by participating in our study.

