Expectant mothers assigned to the intervention group will watch the 10 Amandla Mama videos and their partners will receive the same 10 Amandla Mama videos via the social media platform, WhatsApp or short messaging service (SMS). The expectant mothers will be asked to provide the researchers with their contact details and the contact details of their partners. Partners who agree to participate in the study and who provide informed consent will receive the Amandla Mama videos by SMS or WhatsApp. The control group will receive existing treatment as usual-antenatal care only.

After 3 months, knowledge, behavioral intent, and user satisfaction surveys will be administered telephonically to all participants. The follow-up is conducted after 3 months to test long-term retention providing a better predictor for ongoing change. The research assistants under supervision of the researchers, will administer the telephonic survey. Data collected from participants who discontinue with or deviate from the study will not be used.

Surveys for the expectant mothers consist of a total of 61 questions: 10 background questions, 15 behavioral intention questions, 30 knowledge questions and 8 user satisfaction questions (refer to Additional file 1: Annexure 2). Surveys for partners consist of a total of 63 questions: 8 background questions, 18 behavioral intention questions, 30 knowledge questions and 8 user satisfaction questions (refer to Additional file 1: Annexure 3). The user-satisfaction questions, which consider how satisfied the participants are with the Amandla Mama videos, will only be administered to participants in the intervention group. All Phase 2 study participants will receive ZAR 100 to compensate them their time and expenses incurred by participating in our study.

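### Both arms share two clinics and partners' videos can be forwarded, yet no described item shows whether controls saw them; Phase 1 reviewers may also enter Phase 2

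*Protocol article*

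**What the plan says.** - **Allocation.** The Study site section names two community health centres. Under Phase 2 sampling & data collection, each consenting participant takes the next row of a randomisation table, so both arms attend the same clinics.
- **Delivery.** For partners: "Partners who agree to participate in the study and who provide informed consent will receive the Amandla Mama videos by SMS or WhatsApp". Intervention mothers are said only to watch the ten videos, with no device or place given. The satisfaction items in mock Table 2 include ease and time of download. The outcome survey is by telephone after three months.
- **Eligibility.** Study population: "There are no specific exclusion criteria beyond the inclusion criteria". Phase 1 interviews 10-15 pregnant women at the same sites, with partners also recruited. Feedback from mothers, partners and health workers refines the storyboards (text under Fig. 1).
- **Exposure.** The only video questions described are the eight satisfaction items, which "will only be administered to participants in the intervention group". Phase 2 data analysis names Mom-Connect exposure as a confounder. Neither that section nor mock Tables 1 to 3 mention controls' exposure to the study videos.
- **Deviators.** Phase 2 sampling & data collection says that data from participants who discontinue or deviate will not be used. Phase 2 data analysis invokes intention to treat.

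**The concern.** The intervention is information in a form that is easy to pass on. The Background stresses the small file size, and the Discussion the flexible distribution. Women in both arms meet at the same antenatal services, and a video received by an intervention partner can reach a control household during the three months before the outcome. Phase 1 contributors already know the storyboards, and the stated eligibility rule does not keep them out of the control arm.

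Both routes act in one direction: they raise the control score and shrink the difference. If the trial finds little or no difference, the sponsor will want to know whether the videos do not work or whether controls had seen them. Nothing described in the article would supply that information. The authors accept that outside information matters, since they name Mom-Connect, but the study's own videos are not treated in the same way.

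**Working it through.** **Step 1. The plan's own figure.** Inputs from Phase 2 sampling & data collection: "We use a 0.05 level of significance", "a power of 0.9 with a two tailed test for significance", and "Power: 0.9, Alpha 0.05, Allocation N1/N2: 1, p1 = 0.43, p2 = 0.61". With the pooled z-test for two proportions,

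n per arm = [z(0.975)·√(2·p̄·q̄) + z(0.90)·√(p1·q1 + p2·q2)]² / (p2 − p1)²,

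where p̄ = 0.52, 2·p̄·q̄ = 0.4992 and p1·q1 + p2·q2 = 0.2451 + 0.2379 = 0.4830:

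(1.960 × 0.7065 + 1.282 × 0.6950)² / 0.0324 = 159.8, so 160 per arm.

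The stated 140 is not reproduced. Continuity-corrected (171), unpooled (157) and arcsine (161) versions do not give it either. A one-sided test gives 131, which rounds up to 140 by tens, although the text says two-tailed. That is a separate matter. Here it means only that 140 per arm has 85.8% two-sided power before any dilution. The drop-out step does reproduce: 140 × 1.5 = 210 per arm, and 2 × 210 = 420.

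**Step 2. Sharing between arms.** The document gives no rate, so the share c of controls who see the videos is an assumption. Each such control is assumed to gain the full 18 points, which is a worst case for second-hand viewing.

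- Control rate = 43 + 18c
- Difference = 18(1 − c)
- Ratio = 61 / (43 + 18c)

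| c | Control rate | Difference (points) | Ratio | Power, 140 analysed per arm | Power, 210 analysed per arm | n per arm for 90% |
|---|---|---|---|---|---|---|
| 0% | 43.0% | 18.0 | 1.42 | 85.8% | 96.1% | 160 |
| 10% | 44.8% | 16.2 | 1.36 | 77.8% | 91.7% | 198 |
| 20% | 46.6% | 14.4 | 1.31 | 67.8% | 84.4% | 250 |
| 30% | 48.4% | 12.6 | 1.26 | 56.3% | 73.9% | 326 |

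Power is two-sided at 0.05 by the plan's own method. The 210 column assumes no drop-out. The article describes the 43% and 61% as intention scores, while knowledge is the primary outcome, so the table shows scale and does not forecast the knowledge result.

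**Step 3. Phase 1 carry-over.** At most 15 women are interviewed, or 15/420 = 3.6%. The number of partners is not stated; with one each, the ceiling is 30/420 = 7.1%. Under 1:1 allocation about half would be controls:

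- 15 women: 7.5/210 = 3.6% of controls; 18 × 0.036 = about 0.6 points.
- 30 people: 15/210 = 7.1% of controls; 18 × 0.071 = about 1.3 points.

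Both figures assume that every contributor re-enrols and that a storyboard has the full effect of a finished video.

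**The case against.** The strongest reply is that this is largely silence in a condensed article, that the size is assumed, and that the bias is conservative. Much of that stands, and several stronger readings should be set aside.

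- **That controls are never asked.** A reader might infer this, but the article gives only question counts and refers to annexures that are not shown. Mock Table 1 names eight background variables, and Mom-Connect makes nine of the mothers' ten background questions, so one is unaccounted for. The supportable statement is that no described item, confounder or table captures control exposure.
- **That all videos go to private phones.** This is explicit for partners only. The download items suggest phone delivery to mothers but do not establish it.
- **That Phase 1 carry-over is a serious threat.** Contributors are few and commented on storyboards. The women would have to be expectant again or still when Phase 2 recruits.
- **That health workers carry the messages to controls.** The plan says "Additionally, in-depth interviews will be conducted with 10-15 health workers at the study sites", but those eligible include managers and district staff. Nothing shows that contributors deliver control care differently.
- **That re-viewing defeats the retention claim.** Retention is given only as the reason for the follow-up time. The objectives concern change after watching the series, and re-viewing would be part of the intervention as delivered.
- **That objective ii could not be answered.** At an assumed 30% with full effect, 12.6 of 18 points remain. The as-randomised comparison with usual care stays valid.

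The objection does not remove the stated eligibility rule, the shared clinics with a forwardable delivery route, or the absence of any described measure of control exposure. It also adds a useful warning. Exposure data combined with the rule on deviators could be used to drop exposed controls after randomisation, which would be worse than dilution.

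**Conclusion.** The concern holds as a cheap improvement to the design. The plan leaves open two routes by which controls may meet the content, and it describes no means of seeing whether they did. Sharing is the route that matters: each 10% of controls who gain the full effect costs 1.8 points of the planned 18. Phase 1 carry-over has a ceiling of about 0.6 to 1.3 points. The sharing rates are assumptions, full effect from second-hand viewing is a worst case, and the annexed questionnaires could not be checked. The consequence is attenuation and a null result that is hard to interpret; the comparison itself is not invalid.

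**What to change.** 1. **Study population:** replace the statement of no further exclusions with one that makes people interviewed in Phase 1, and their partners, ineligible for Phase 2.
2. **At delivery:** ask intervention recipients not to forward the videos until follow-up ends.
3. **Three-month call:** after all outcome items, ask participants in both arms whether they have seen any Amandla Mama video and how many. Report the answers by arm beside the unchanged as-randomised primary result. If the annexed questionnaires already contain such an item for controls, say so and add the by-arm report.
4. **Rule on deviators:** state that a control who saw the videos is not a deviator, so that those data stay in the analysis.

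The cost is two or three extra questions and the loss of at most about 30 eligible people at high-volume clinics. The questions may disclose the arm to the interviewer, so they must come last.
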